**Figure 2 f2:**
[figure not shown]
Flow chart of the study design. BL-1, a proprietary herbal formulation developed by West China Hospital of Sichuan University; LARS, low anterior resection syndrome; FAS, full analysis set; PPS, per-protocol set; SAS, safety set.

#### Emergency treatment

2.5.3

Participants who are unable to tolerate their LARS symptoms or are dissatisfied with the treatment effects will, at their request, have the option to receive loperamide Hydrochloride Capsules (Imodium, Xi’an Janssen Pharmaceutical Co., LTD) (17), the guideline-recommended first-line medication for LARS. Detailed recording of medication dosages and treatment duration will be maintained in the case report forms (CRFs).

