**Methods/design:**

The study will be conducted as a randomized, double-blind, placebo-controlled trial, comprising a 4-week intervention phase and a subsequent 2-week follow-up period. A total of 234 patients with LARS, aged 18 to 75 years, are planned to be enrolled in this study. Eligible participants will be randomized to receive either the BL-1 group or placebo group in a 1:1 ratio. Participants in the experimental group will receive BL-1 formulation, whereas those in the placebo group will receive an indistinguishable BL-1 placebo. The primary outcome measure is the change in LARS score from baseline to week 4. Secondary outcome measures encompass: (a) stool frequency and consistency (assessed via the Bristol Stool Scale); (b) severity of fecal incontinence (evaluated using the Wexner Anal Incontinence Scale); (c) QOL, measured with the European Organization for Research and Treatment of Cancer QOL questionnaire and the Karnofsky Performance Status score; and (d) other patient-reported outcomes. Safety will be monitored continuously throughout the treatment, with assessments including the incidence of adverse events and laboratory abnormalities.

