#### Prohibited concomitant medications/treatments

2.5.4

During the trial, with the exception of medications/treatments permitted by the protocol, the following interventions that may interfere with study assessments are prohibited, including but not limited to: (1) anti−diarrheal agents, such as ramosetron, ondansetron, and compound diphenoxylate tablets; (2) TCM therapies for LARS, including oral administration of other Chinese herbal medicines, acupuncture, acupoint application, moxibustion, acupoint catgut embedding, among others; and (3) other Western medical interventions, such as neuromodulation, pelvic floor rehabilitation therapy, and transanal irrigation.

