#### Primary outcomes

2.7.1

The primary outcome is defined as the change in LARS score between baseline and week 4. The degree of LARS symptom severity will be measured using the LARS symptom severity score (LARSS) (20). The LARSS is assessed across five key domains: incontinence for flatus, incontinence for liquid stool, stool frequency, clustering of bowel movements, and urgency. The summation of individual item scores yields the total score, which is subsequently categorized according to predefined severity levels. The LARSS will be used to stratify disease severity into three levels: normal (score ≤ 20), mild (21 ≤ score ≤ 29), and severe (30 ≤ score ≤ 42). Treatment response will be evaluated based on changes in severity from original (baseline) level. Patients showing no improvement or any deterioration (e.g., from mild to severe) will be classified as non-responders, while those demonstrating improvement will be categorized as responders (e.g., from severe to mild, from severe to normal, and from mild to normal). The response rate is defined as the ratio of responding participants to the total number of randomized participants, multiplied by 100%.

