#### Secondary outcomes

2.7.2

Secondary endpoints will include the following: (a) changes in the LARSS from baseline to weeks 2 and 6; (b) the proportion of patients demonstrating improvement in bowel dysfunction across the three assessment time points (weeks 2, 4, and 6). Clinical transitions in LARS severity will be assessed using the LARSS, specifically documenting the number of patients transitioning from severe to mild, mild to none, and severe to none; (c) stool frequency, which will be assessed by recording the average number of spontaneous bowel movements per day or per week for the patients at weeks 0, 2, 4, and 6; (d) stool consistency, which will be assessed by recording the average daily or weekly stool consistency at weeks 0, 2, 4, and 6 (21); (e) anal function, which will be assessed using the Wexner anal incontinence scale score at weeks 0, 2, 4, and 6 (22); (f) QOL, which will be assessed at weeks 0, 4, and 6 using the cancer-specific European Organization for Research and Treatment of Cancer scale (EORTC QLQ-C30) (23); (g) functional status, which will be assessed using the Karnofsky Performance Status (KPS) score at weeks 0 and 4; and (h) safety, which will be evaluated as follows: 1) biochemical indices, including liver function (alanine aminotransferase and aspartate aminotransferase), kidney function (blood urea nitrogen and creatinine); 2) electrocardiographic assessment of cardiac electrical activity; 3) adverse events (AEs): any unfavorable symptoms (including rash, constipation) documented during treatment. AE incidence: (number of patients experiencing AEs/total number of patients) × 100%; 4) severe AEs.

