Continuous variables such as LARSS, EORTC QLQ-C30, and KPS will be subjected to normality hypothesis tests. Continuous variables will be reported as mean (SD) or median (IQR), depending on distributional assumptions assessed through normality tests. Simple and multiple linear regression models will be employed to assess group differences between the BL-1 and placebo groups for both primary and secondary continuous outcomes. Two pre-specified adjusted analyses will be conditionally performed, contingent upon meeting prespecified conditions in the data. The first preadjusted analysis will incorporate *a priori* selected baseline variables, namely age, sex, smoking history, alcohol consumption status, radiotherapy history, and surgical characteristics. The second preadjusted model will further include concomitant treatment as an additional covariate, which is considered a prognostic factor unaffected by treatment assignment. Prespecified subgroup analyses will include the TNM staging of rectal cancer, baseline LARS severity, and three types of surgical resection: low, medium, and high. Categorical variables will be presented as frequencies and corresponding percentages. Primary and secondary categorical outcomes will be analyzed using chi-square tests, supplemented by logistic regression when conditions warrant its application. Adjusted analyses will be extended to categorical outcomes using the same predefined set of covariates as employed in the continuous outcome analyses.

The statistical software employed for data analysis will be IBM SPSS Statistics, Version 29.0. Estimates of intervention effects will be reported as point estimates accompanied by 95% confidence intervals, with a two-tailed *P* value threshold of < 0.05 defining statistical significance.

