
Prompted by the limited treatment options in current guidelines and documented AEs of available therapies, our team undertook a comprehensive investigation into the pathogenesis of LARS through the lens of TCM, while also systematically reviewing the evidence for TCM and acupuncture efficacy and safety (data unpublished). The current evidence regarding LARS treatments is substantially constrained by methodological quality, necessitating rigorously designed investigations to validate TCM’s therapeutic role. Accordingly, we employed a randomized, double-blind, placebo-controlled design to assess the therapeutic potential and safety of the BL-1 prescription in patients with LARS. The key pathogenic mechanism of LARS is that the disease remains in Yangming, and dampness, phlegm and stasis are intertwined. Therefore, this study aims to assess the therapeutic application of BL-1 in managing LARS across a 4-week intervention period. The clinical effectiveness and safety of BL-1 for the treatment of LARS will be evaluated on the basis of the daily frequency of diarrhea, stool consistency, Wexner anal incontinence score, LARSS, LARS response rate, QOL, KPS score, and reduction in the need for acute treatment.

The following limitations should be considered when interpreting the results of this investigation. First, a notable constraint is the absence of validated objective measures for standardized assessment of LARS outcomes. Inter-individual variability and perceptual differences in symptom reporting may introduce substantial variance in documented drug efficacy profiles. Second, treatment dissatisfaction or intolerability of LARS symptoms may adversely affect patient adherence, thereby increasing the dropout rate. Third, as some participants may reside in other provinces, the quality control of the “direct drug delivery to participants” process requires further refinement. To enhance patients’ comprehensive trial awareness, our study staff received specialized training in establishing effective communication channels and building therapeutic rapport.

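### Reduced need for rescue treatment is named as an effectiveness measure but is not an endpoint, and an undefined concomitant-treatment covariate may bring rescue loperamide into an adjusted model

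*Protocol article*

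**What the plan says.** All references are to the protocol article.

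- **Rescue rule (2.5.3, Emergency treatment).** Loperamide is available to participants who cannot tolerate their LARS symptoms or who are "dissatisfied with the treatment effects will, at their request, have the option to receive loperamide Hydrochloride Capsules". The section adds: "Detailed recording of medication dosages and treatment duration will be maintained in the case report forms (CRFs".
- **Other treatments (2.5.4).** The rule is that "with the exception of medications/treatments permitted by the protocol, the following interventions that may interfere with study assessments are prohibited". The list covers other antidiarrhoeals, TCM therapies for LARS, and interventions such as neuromodulation, pelvic floor rehabilitation and irrigation.
- **Effectiveness measures (3, Discussion).** The list on which effectiveness and safety are to be judged ends "LARS response rate, QOL, KPS score, and reduction in the need for acute treatment".
- **Declared endpoints.** Section 2.7.1 gives the change in LARS score to week 4 and a response rate: "The response rate is defined as the ratio of responding participants to the total number of randomized participants, multiplied by 100". Section 2.7.2 lists items (a) to (h), among them "the proportion of patients demonstrating improvement in bowel dysfunction across the three assessment time points (weeks 2, 4, and 6". None of them is rescue use. The Abstract's outcome list ends "Karnofsky Performance Status score; and (d) other patient-reported outcomes".
- **Second adjusted model (2.11).** It adds "concomitant treatment as an additional covariate, which is considered a prognostic factor unaffected by treatment assignment". Section 2.11 carries the same covariates over to the categorical outcomes. Both adjusted analyses are described as conditional.

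**The concern.** There are two linked problems.

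**A measure without an endpoint.** The Discussion commits the trial to judging BL-1 partly on how much acute treatment is needed. The endpoint sections do not define that measure, give it a time point or compare it by arm. It matters for interpretation because section 2.5.3 itself calls loperamide the guideline first-line drug. A participant who improves after taking it counts as improved in the assigned arm. If placebo patients take it more often and it works, the LARS-score and response differences shrink. Rescue use by arm is what would let a reader tell a diluted result from a null one.

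**A covariate premise that may be false.** Rescue is triggered by dissatisfaction with the assigned treatment, so it is a consequence of treatment. If concomitant treatment includes it, the second adjusted model conditions on a post-randomisation outcome of treatment while asserting the opposite. A real effect could then appear to weaken on adjustment.

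**Working it through.** **1. Endpoint cross-check.** Each item in the Discussion's list, set against sections 2.7.1 and 2.7.2:

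| Discussion item | Declared endpoint |
|---|---|
| Daily frequency | 2.7.2 (c) |
| Stool consistency | 2.7.2 (d) |
| Wexner score | 2.7.2 (e) |
| LARS score | 2.7.1; 2.7.2 (a) |
| Response rate | 2.7.1; 2.7.2 (b) |
| QOL | 2.7.2 (f) |
| KPS | 2.7.2 (g) |
| Need for acute treatment | none |

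I read acute treatment as the loperamide of section 2.5.3, the only on-demand treatment the article describes.

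**2. What concomitant treatment can mean.** Section 2.11 gives its baseline covariates in the first adjusted model: age, sex, smoking, alcohol, radiotherapy history and surgical characteristics. Concomitant treatment is added separately in the second, so the natural reading is treatment taken during the trial. Section 2.5.4 prohibits the other LARS treatments, which leaves loperamide as the only LARS drug named as permitted. The term is not defined, so this remains an inference.

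**3. Scale of the planned effect.** Section 2.8 gives means of 9.75 and 8.55 (difference 1.20), SD 2.5, two-sided alpha 0.05 and power 0.90. The normal formula gives 2 × (1.960 + 1.282)² × 2.5² / 1.20² = 91.2, so 92 per group. The t-test version gives 92.18, so 93, as stated. Then 93 / 0.80 = 116.25, so 117, also as stated. These figures reproduce; they are used below only to set the scale.

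**4. Effect of adjusting for rescue (illustration).** Taken from section 2.8: difference 1.20, SD 2.5. Assumed: 20% rescue overall, loperamide with no effect, and rescue taken by the 20% with the highest dissatisfaction score, which has correlation ρ with poor improvement. In a linear model,

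adjusted difference = unadjusted difference − |rescue coefficient| × (placebo rescue rate − BL-1 rescue rate).

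| ρ | Rescue, BL-1 vs placebo | Rescue coefficient | Adjusted difference | Change |
|---|---|---|---|---|
| 0.3 | 18.0% vs 22.0% | −1.31 | 1.20 − 1.31 × 0.040 = 1.15 | −4% |
| 0.5 | 16.7% vs 23.3% | −2.19 | 1.20 − 2.19 × 0.066 = 1.06 | −12% |
| 0.8 | 14.7% vs 25.3% | −3.50 | 1.20 − 3.50 × 0.106 = 0.83 | −31% |

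The unadjusted difference stays at 1.20 throughout. Depending on how the dissatisfaction score is standardised and on rounding, the last two rows come out at 1.05 to 1.06 and 0.83 to 0.84.

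**5. A second set of assumptions.** Here rescue is taken when underlying improvement plus noise falls below 6 or 7 points, giving rescue in about 10–17% on BL-1 and 19–30% on placebo.

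| Loperamide adds | Unadjusted | Adjusted |
|---|---|---|
| 0 points | 1.21 | 0.75–0.85 |
| 2 points | 0.95–1.02 | 0.74–0.84 |
| 4 points | 0.70–0.83 | 0.74–0.84 |

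The adjusted figure is below the rescue-free 1.20 in every case. When loperamide is strong, it lies close to or slightly above the unadjusted figure. So the adjusted model neither recovers the effect without rescue nor estimates the effect regardless of rescue.

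**The case against.** The strongest reply has four parts.

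- **The Discussion does not define endpoints.** One clause could be deleted, and rescue use could be tabulated from the CRFs under an analysis plan that is not shown. Deletion would indeed remove the inconsistency. It would also drop a measure the authors say they will use and whose data they already collect. The two lists disagree within the article itself, so this is not simply a detail left to another document. The assessment schedule (Figure 1) is not shown; even if it lists rescue recording, section 2.7.2 still omits the endpoint.
- **The covariate point is hypothetical.** Loperamide has its own heading, apart from concomitant medications, and the stated premise would suit baseline or non-LARS treatment. This stands as a limit: on that reading the second problem disappears and the first remains.
- **The magnitudes are assumed.** Correct. The rescue rates, correlations and loperamide effects are not in the documents, and results vary with them.
- **The trial is exploratory and the model is secondary.** Also correct, and it limits the consequence.

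A reader might go further and infer that rescue undermines the primary comparison, or that rescued participants must count as non-responders. The documents do not support either. Analysing all participants regardless of rescue is a legitimate choice, and crediting improvement under rescue to the assigned arm is part of that choice. A non-responder sensitivity analysis is optional.

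**Conclusion.** The point holds in two parts of unequal strength.

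The first is unconditional: an effectiveness measure named in the Discussion has no counterpart among the declared endpoints, although its data are collected.

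The second is conditional on concomitant treatment including loperamide. If it does, the stated premise conflicts with the rescue rule, and the adjusted BL-1 effect is biased, toward no difference relative to the rescue-free effect when rescue is commoner on placebo. The size is unknown. Under the assumptions shown with an inert rescue drug, the adjusted difference is 1.15 to 0.75 against a true 1.20. The same flaw would carry into the adjusted response analysis through the shared covariates.

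It would be tempting to say that section 2.11 definitely adjusts for rescue, or that the trial's main result is biased. The term is undefined, and only a conditional secondary model is touched, so neither follows. This should be corrected, but it does not threaten the primary analysis.

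**What to change.** 1. In section 2.7.2, add loperamide use to week 4 as a secondary endpoint compared by arm: any use, and total dose or days of use, from the existing CRF record. Check that the CRF allows use up to week 4 to be separated from use during follow-up; the article does not say.
2. In section 2.11, restrict concomitant treatment to treatments present at baseline, or explicitly exclude loperamide taken after randomisation. Apply this to both the continuous and the categorical adjusted models.

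The rescue rule, the primary outcome and the main analysis regardless of rescue do not change.

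The cost is a protocol amendment with ethics re-approval and a registry update (section 2.12), made while 92 of 234 participants (39%) are already enrolled (section 2.2). The change adds one secondary comparison and relies on data the CRFs already hold. Because assignment stays masked until database lock (section 2.6), it can still be specified before results by arm are known.

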#### Prohibited concomitant medications/treatments

2.5.4

During the trial, with the exception of medications/treatments permitted by the protocol, the following interventions that may interfere with study assessments are prohibited, including but not limited to: (1) anti−diarrheal agents, such as ramosetron, ondansetron, and compound diphenoxylate tablets; (2) TCM therapies for LARS, including oral administration of other Chinese herbal medicines, acupuncture, acupoint application, moxibustion, acupoint catgut embedding, among others; and (3) other Western medical interventions, such as neuromodulation, pelvic floor rehabilitation therapy, and transanal irrigation.

### Randomization, allocation concealment, and blinding

2.6

The randomization schedule for both participants and investigational products was generated using SAS software (version 9.4). Subject randomization and drug allocation will be implemented through the Central Randomization System V5.0 (provided by Beijing Medfuture Technology Co., Ltd.). Eligible patients will be randomized in a 1:1 ratio to receive either the BL-1 group or the placebo group. Simultaneously, the dosage form, properties, odor, appearance, packaging, labeling, and identification of the placebo will be matched with those of the treatment group, and clinical pharmacists prepared the corresponding medications using random numbers to implement allocation concealment for bias minimization (18). All participants and investigating clinicians will remain masked to treatment assignment throughout the trial duration until the final database lock. Designated personnel from the Evidence Based Medicine Centre of West China Hospital will have exclusive access to the randomization list and are mandated to maintain confidentiality until trial completion and full data collection, unless unblinding is necessitated by serious adverse events.

Unblinding of a participant’s assigned intervention will constitute grounds for withdrawal from the study, and the case will be documented accordingly. If 20% or more of the required sample size has their assigned intervention disclosed, the trial can be considered to have failed in maintaining blinding for participants (19). To uphold objectivity and minimize potential bias from investigators and participants, the statistical analysis for this trial will be performed by an independent third party under a blinded manner.

### Outcomes

2.7

#### Primary outcomes

2.7.1

The primary outcome is defined as the change in LARS score between baseline and week 4. The degree of LARS symptom severity will be measured using the LARS symptom severity score (LARSS) (20). The LARSS is assessed across five key domains: incontinence for flatus, incontinence for liquid stool, stool frequency, clustering of bowel movements, and urgency. The summation of individual item scores yields the total score, which is subsequently categorized according to predefined severity levels. The LARSS will be used to stratify disease severity into three levels: normal (score ≤ 20), mild (21 ≤ score ≤ 29), and severe (30 ≤ score ≤ 42). Treatment response will be evaluated based on changes in severity from original (baseline) level. Patients showing no improvement or any deterioration (e.g., from mild to severe) will be classified as non-responders, while those demonstrating improvement will be categorized as responders (e.g., from severe to mild, from severe to normal, and from mild to normal). The response rate is defined as the ratio of responding participants to the total number of randomized participants, multiplied by 100%.

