#### Participant inclusion criteria

2.4.2

The key inclusion criteria are as follows: (a) aged 18–75 years; (b) a preoperative clinical diagnosis of rectal cancer with a TNM stage I–III; (c) patients meeting the 2020 LARS diagnostic criteria with a LARS score ≥ 20; (d) transanal defecation frequency ≥ 4 times/day; (e) rectal cancer anal sphincter preservation surgery (including preventive stoma retraction surgery) performed at least one month prior; (f) a Karnofsky score > 60 and an expected survival > 6 months; (g) patients with basic communication skills and understanding who are willing to cooperate with the examination, treatment and follow-up; and (h) patients who have provided signed informed consent following a detailed explanation of the trial.

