### Sample size

2.8

On the basis of preliminary results from the pilot trial, the BL-1 treatment group had a score reduction of 9.75 ± 2.30 points, whereas the placebo control group had a reduction of 8.55 ± 2.84 points. The overall mean change in the LARSS was assumed to be 9.75 for the BL-1 group and 8.55 for the placebo group. The variances of the two groups were homogeneous, with a standard deviation of 2.5. A superiority design was adopted, with a two-sided test level set at α = 0.05 and a test power of 1-β = 0.9. A sample size calculation was performed based on a balanced design (1:1 allocation), indicating that 93 participants are required per group. Adjusting for an anticipated withdrawal rate below 20% (24), the target enrollment was planned as 117 patients per group, but the intention−to−treat (ITT) and per−protocol set (PPS) analysis sets will be determined based on the final sample size and completion data at trial end. The data collected in this trial will inform future sample size calculations and provide a foundation for the design of subsequent large-scale clinical trials.

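### The band-crossing response rate depends far more on the starting LARS score than on treatment, and the planned analysis does not adjust for that score

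*Protocol article*

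**What the plan says.** Section 2.7.1 sets the primary outcome as a continuous measure: "The primary outcome is defined as the change in LARS score between baseline and week 4". The same section then bands the score as "normal (score ≤ 20), mild (21 ≤ score ≤ 29), and severe (30 ≤ score ≤ 42" and adds a response rate: "Treatment response will be evaluated based on changes in severity from original (baseline) level". A move to a better band is a response: "while those demonstrating improvement will be categorized as responders (e.g., from severe to mild, from severe to normal, and from mild to normal". Everything else is non-response: "Patients showing no improvement or any deterioration (e.g., from mild to severe) will be classified as non-responders".

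Section 2.7.2 (b) uses the proportion improved at weeks 2, 4 and 6 as a secondary endpoint, "specifically documenting the number of patients transitioning from severe to mild, mild to none, and severe to none".

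Section 2.8 bases the sample size on the mean change: "the BL-1 treatment group had a score reduction of 9.75 ± 2.30 points, whereas the placebo control group had a reduction of 8.55 ± 2.84 points", with a common SD of 2.5 and 93 evaluable patients per group.

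Section 2.11 compares categorical outcomes by chi-square, with logistic regression where conditions allow. Its adjustment set is age, sex, smoking, alcohol, radiotherapy history and surgical characteristics. Baseline LARS score is not in it. Baseline severity appears only as a subgroup.

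**The concern.** The rule sets no minimum improvement, only the crossing of a cut-off. A fall from 30 to 29 is a response. A fall from 42 to 30, at 12 points larger than the mean fall planned for BL-1, is not, and neither is a fall of 8 points from 29 to 21.

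The plan expects falls of roughly 9 points in both arms. Patients who start low in a band will then nearly all respond whatever they receive, and patients at the top of the severe band will mostly not. Neither group says much about treatment. If the analysis ignores the starting score, that variation stays in the comparison as noise. A null result on the response rate could then be read as evidence against BL-1 when the comparison had little chance of showing the planned effect. This matters because section 3 lists the response rate among the measures of effectiveness, and section 2.8 says the data will inform later trials.

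**Working it through.** **Sample size first.** Difference 9.75 − 8.55 = 1.20, SD 2.5, two-sided 0.05, power 0.90. The normal formula gives n = 2 × (1.960 + 1.282)² × 2.5² / 1.20² ≈ 91.2, so 92. The t-based version gives 93 (power 0.903). 93 / 0.8 = 116.25, so 117. The plan's 93 and 117 are reproduced.

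**Fall needed for response.** For baseline b from 21 to 29 the fall needed is b − 20. For b from 30 to 42 it is b − 29. That is 1 to 9 points in the mild band and 1 to 13 in the severe band. The entry rule in section 2.4.2 is "patients meeting the 2020 LARS diagnostic criteria with a LARS score ≥ 20", so a patient entering at exactly 20 is already in the normal band and cannot respond.

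**Response by baseline score.** Assume the change is normal with mean 9.75 (BL-1) or 8.55 (placebo) and SD 2.5, independent of baseline. Then P(response | b) = 1 − Φ((fall needed − mean) / 2.5).

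| Baseline | Fall needed | z, BL-1 / placebo | Response, BL-1 / placebo |
|---|---|---|---|
| 21 or 30 | 1 | −3.50 / −3.02 | >99% / >99% |
| 25 or 34 | 5 | −1.90 / −1.42 | 97% / 92% |
| 29 or 38 | 9 | −0.30 / 0.18 | 62% / 43% |
| 40 | 11 | 0.50 / 0.98 | 31% / 16% |
| 42 | 13 | 1.30 / 1.78 | 10% / 4% |

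Within the severe band, response in either arm drops by about 90 percentage points or more as baseline goes from 30 to 42. The largest gap between arms at any baseline score is 19 points. Response also jumps from 62% / 43% at 29 back to over 99% at 30. A 0.5-point continuity correction (14% / 6% at 42), or the arm-specific pilot SDs with that correction (12% / 8% at 42), leaves the pattern unchanged.

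**Power of the pooled comparison.** The article gives no baseline distribution, so one has to be assumed. With baseline uniform over 21–42, average response is 78.7% vs 70.4%, a difference of 0.083 with mean 0.745. The standard error under no difference is √(2 × 0.745 × 0.255 / 93) = 0.064, and it is also 0.064 under the difference. Power = Φ((0.083 − 1.96 × 0.064) / 0.064) ≈ 25% (24% with the continuity correction).

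Other assumptions were uniform over 20–42, the mild band alone, the severe band alone, and normal distributions with mean 28–38 and SD 3–5. Across all of these, response is about 61–93% on BL-1 and 48–86% on placebo, and power with 93 per arm is about 21–43%. Baseline score explains about 19–53% of the variance in response, and arm about 0.7–1.7%.

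**Adjusted ordinal analysis.** In a simulation with baseline uniform over 21–42 and 93 per arm, power was about 24% for the unadjusted crossing rule, 18% for an unadjusted three-level proportional-odds model, and 54% for the same model with baseline score included. The gain comes from the baseline adjustment, not from the ordinal scale alone.

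**The case against.** The strongest reply is that the response rate is only a supplementary summary. The trial is sized at 90% power on the mean change, and low power for an extra summary is not a fault in the design. Unequal distance to a cut-off is inherent in any banded scale. Randomisation balances baseline scores in expectation, so the chi-square test keeps its type I error. All of this stands. The defect is one of precision and interpretation, not of bias, and it does not reach the primary analysis. It remains worth correcting because the rule sits under the primary-outcome heading, section 2.11 speaks of primary categorical outcomes, and the listed covariates leave out the variable that matters most.

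Four stronger readings are tempting but not supported.

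- A reader might infer that worsening is hidden. The response rate does pool deterioration with no change, a severe patient has no worse band to enter, and the listed transitions are all improvements. But the primary outcome and secondary endpoint (a) are score changes, which carry worsening. The plan's own figures also put the probability of a rise in score below 0.15% in either arm.
- A reader might infer that the change information is thrown away. It is the primary outcome.
- A reader might conclude that baseline explains most of the variation in response. That depends on the assumed distribution, and in most of those tried the share is under half. The supportable statement is relative: baseline matters far more than arm.
- A reader might think a fixed-point cut is the remedy. Its advantage depends on where it is placed. A cut at 9 points, close to the midpoint of the planned means ((9.75 + 8.55) / 2 = 9.15), gives about 75% power, while a cut at 5 points gives about 32%. The article offers no basis for choosing one.

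Section 1 reports about 65% efficacy for BL-1 in a pilot, but without a definition, so it cannot fix the baseline distribution. The assumed distribution closest to it with the continuity correction (mean 38, SD 3: 67% vs 54%) gives about 43% power, the top of the range.

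**Conclusion.** The concern holds for the band-crossing response rate in sections 2.7.1 and 2.7.2 (b), and only there. The dependence on starting score follows from the cut-offs without any assumption: 1 to 13 points are needed. Its size follows from the section 2.8 figures, if changes are normal and independent of baseline: over 99% in both arms at 21–22 or 30–31, down to 10% vs 4% at 42. The power figure of about 20–45% with 93 per arm also rests on an assumed baseline distribution. The continuous primary outcome and the sample size of 93 (117 enrolled) per group are sound on this point. The change should be made, but the main result does not depend on it.

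**What to change.** 1. Keep the three bands and state that the response rate is a secondary outcome.
2. Analyse severity level at weeks 2, 4 and 6 as an ordered three-level outcome in a proportional-odds model that includes baseline LARS score. At minimum, add baseline LARS score to the logistic model for response. Because response falls across each band and jumps back at 30, a single straight-line term in that logistic model fits poorly, so baseline band should be entered as well.
3. Show the full baseline-to-visit shift table by arm, including no change and mild to severe, instead of the three improving moves alone.

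This costs a change of wording, one model and one table, and needs no new data. It should be fixed before unblinding. The downsides are small: an odds ratio is less familiar than a response rate, and the proportional-odds assumption has to be checked.
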